| Maternal feeding practices and beliefs – Infant Feeding Style Questionnaire (IFSQ) |         |         | X         | X        |
| Maternal depression – CES-D                                                        | X       |         | X         | X        |
| Self-reported physical health                                                      |         |         |           | X        |

|                                                                         |   |   |   |   |
|-------------------------------------------------------------------------|---|---|---|---|
| Child Safety Outcomes                                                   |   |   |   |   |
| Safe sleep practices – Fowler                                           | X |   |   | X |
| Child safety practices – Framingham Safety Survey                       |   |   |   | X |
| Stress-Support Moderators                                               |   |   |   |   |
| Maternal Personality – Mini IPIP                                        | X |   |   |   |
| Family Background – Risky Families Questionnaire                        | X |   |   |   |
| Financial strain/employment – Assorted questions                        | X |   |   |   |
| Discrimination – Schedule of Racist Events                              | X |   |   |   |
| Romantic relationship characteristics – Assorted questions              | X |   | X | X |
| Co-parent relationship characteristics – Coparenting relationship scale |   |   |   | X |
| Social support – Social Provisions Scale                                | X |   |   |   |
| Family routines - Confusion, Hubbub and Order Scale (CHAOS)             |   |   | X |   |
| Demographics and Health History                                         |   |   |   |   |
| Family demographics, maternal/infant health                             | X |   |   |   |
| Intervention-Related Variables                                          |   |   |   |   |
| Co-parent involvement in intervention                                   |   | X | X |   |
| Implementation quality                                                  |   | X | X |   |

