## **7. Data and Specimen Management**

a. Describe the data analysis plan, including any statistical procedures:

☐  
N/A

Data analysis will be led by [name], who has expertise in the analysis of longitudinal data. [name]., Assistant Research Scientist and Statistician at CFR, will provide statistical support for the conduct of analyses. All primary statistical analyses will invoke the intent-to-treat paradigm, analyzing data based on randomized assignment. Missing data will be handled using full-information maximum likelihood methods, which use all available information to estimate parameters, making this approach more efficient and less biased than other methods when data are missing at random. All models considered allow for the inclusion of relevant covariates. Covariates to be considered in refining the analyses, in addition to those described in detail in the proposed analyses below, include demographic factors (e.g., maternal employment and hours worked, gestational diabetes), weight-related factors (e.g., maternal pre- pregnancy weight/BMI, gestational weight gain, maternal smoking), and intervention-related factors (e.g., implementation quality, coparent involvement in intervention). We will also examine (1) infant sex as a covariate, given different growth charts for boys and girls and (2) feeding mode as a covariate, given differences in weight gain between breastfed and formula-fed infants.

**Specific Aim 1: The Effects of Sleep SAAF on Infant Weight and Rapid Weight Gain.** In Specific Aim 1 the primary outcomes are infant weight and changes in weight. BMI is generally assumed to be the standard growth measure for assessing obesity-risk in children age 2 years and older, but there is not one universally accepted measure for children younger than age 2 years. Recent data suggests that infant BMI at age 2 months is more strongly associated with obesity at age 2 years than is weight-for-length. Accordingly, BMI z scores will be our primary outcome, but we will also consider models that examine a range of other weight outcomes, including weight for length z-scores, percentiles, and weight for age z-scores; we anticipate that change across different indices of weight gain will be highly correlated and lead to similar conclusions in tests of program impact as well as tests of potential moderators and the hypothesized mediational model.

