| 
age z-score > +0.67, as described by Ong and Loos. This increase corresponds to crossing adjacent major centile lines on the standard CDC growth charts. The analysis for these rapid weight gain scores will be a repeated measures analysis, assessing the intervention effects on rapid weight gain scores from age 3 weeks up to age 16 weeks. The analysis will use generalized estimating equations (GEE) with a logit link, an extension of logistic regression which allows for repeated measurements on binary data, and will include infant weight adjusted for gestational age as a covariate. Because it is unlikely that within an 16-week period we will have many infants who meet the criteria for rapid weight gain based on the upward percentile crossing approach, we will also calculate conditional weight gain scores (CWG) following the method of Griffiths and colleagues, as described in our recent work.
 
Specific Aim 2: The Effects of Sleep SAAF on Parental and Infant Behaviors that Mediate Effects on Infant Growth. In Specific Aim 2 the primary outcomes are parental behaviors (parental self-efficacy, sleep/soothing practices, feeding practices, family chaos) and infant behaviors (sleep, soothing, and feeding) targeted by the intervention that may mediate effects on infant growth. We examine these effects in several steps.
 
First, we will examine differences between the Sleep SAAF and control groups in these outcomes at two time points post-intervention (8- and 16- weeks postpartum) using the linear mixed-effects model described above. The linear mixed-effects model will include intervention group and infant weight adjusted for gestational age. These analyses will test whether the Sleep SAAF group and the control group differ in these behaviors post-intervention and will be used to identify variables for the formal test of mediation.
 
Second, we will examine whether parent and infant behaviors mediate infant weight outcomes. We will test these hypotheses using structural equation modeling (SEM). The first step in demonstrating mediation is to establish the effects on mediating and distal outcomes, as we described above. We then specify mediators as indirect effects in a path model. Intervention condition will be dummy coded and specified as a predictor of infant and parental behaviors, which in turn predict infant weight and weight gain. The significance of the mediating process will be tested using the Sobel or bootstrapping methods.
 
Specific Aim 3: Moderation of Intervention Effects by Individual and Contextual Factors. In Specific Aim 3 we consider whether individual (depressive symptoms) and contextual (socioeconomic stressors, race-based stressors, romantic relationship characteristics, coparent relationship characteristics, social support) factors at 1 week postpartum moderate program effects. These factors will be included in the analyses described above to determine whether they moderate intervention effects on weight outcomes (Specific Aim 1) and parental and infant behaviors (Specific Aim 2).
 
As an exploratory analysis, we will also evaluate whether the individual and relationship variables differ between the Sleep SAAF group and the control group at 16 weeks postpartum. Doing so will allow us to examine whether improving infant sleep and soothing has secondary benefits for mothers' individual and relationship functioning.
 |                                         |

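### The exploratory 16-week comparison of maternal depressive symptoms and romantic-relationship functioning names no adjustment for the same measure's 1-week score, so as written it is less precise than the collected data allow

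*Supplement*

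**What the plan says.** All references are to the latest protocol version in the Supplement.

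- **Section 7.a, end of Specific Aim 3.** The plan says "we will also evaluate whether the individual and relationship variables differ between the Sleep SAAF group and the control group at 16 weeks postpartum". The stated purpose is to look for secondary benefits to mothers. No model, covariate or baseline term is given.
- **Section 6.a, Table 1.** "Maternal depression – CES-D" and "Romantic relationship characteristics – Assorted questions" are both marked at 1, 8 and 16 weeks. "Co-parent relationship characteristics – Coparenting relationship scale" is marked at 16 weeks only.
- **Section 7.a, Specific Aim 3.** The 1-week values have a different use, namely to test whether "factors at 1 week postpartum moderate program effects".
- **Section 7.a, opening paragraph.** The general clause reads "All models considered allow for the inclusion of relevant covariates", and then "Covariates to be considered in refining the analyses, in addition to those described in detail in the proposed analyses below, include demographic factors". Weight-related and intervention-related factors, infant sex and feeding mode follow. The 1-week value of a maternal outcome does not appear.
- **Section 7.a, Specific Aim 2.** For the behavioural outcomes, "The linear mixed-effects model will include intervention group and infant weight adjusted for gestational age".
- **Section 6.a, Home Visit 1.** Randomisation and the handing over of arm-specific introductory materials are listed as step 1, and the questionnaires as step 2.

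**The concern.** For a repeated symptom or relationship scale, the same scale measured at the start is usually one of the best single predictors of the later score. A 16-week comparison that ignores it carries variance that could be removed with data the trial already collects. The covariate that the stated outcome models do carry, infant weight, has little reason to predict a mother's depressive symptoms or the quality of her relationship.

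At stake is the precision of the exploratory claim about maternal benefit. Chance imbalance in 1-week scores also stays in the unadjusted estimate. The plan already follows the adjusted logic elsewhere: its 16-week infant weight comparison includes infant weight at 1 week.

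**Working it through.** **Inputs**
- Section 7.b: 175 per group, 10% attrition, 80% power, two-sided 5%, detectable d = 0.34. This is the trial's only power figure. It is stated for BMI z scores and the Aim 2 behaviours; none is given for the maternal comparison.
- Section 3: 375 dyads to be recruited.
- The correlation r between 1-week and 16-week scores is not in the documents. I assume 0.3, 0.5 and 0.7.

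**Step 1: the plan's own figure.** A two-sample t-test (noncentral t) gives these detectable effects at 80% power:

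| Analysed per arm | Source | Detectable d | Power at d = 0.34 |
|---|---|---|---|
| 175 | as stated, no loss | 0.300 | 88.7% |
| 157 | 175 × 0.9 | 0.317 | 85.2% |
| 168 | 375 × 0.9 / 2 | 0.307 | 87.4% |
| 135 | 150 × 0.9, from the older protocol version's 150 per group | 0.342 | 79.5% |

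The stated 0.34 is not reproduced from 175 per group, with or without attrition. It matches 135 per arm. The discrepancy is conservative and separate from this point. I use 157 per arm below because it follows from the current text.

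**Step 2: unadjusted comparison.** In SD units, SE = √(2/n) = √(2/157) = 0.113. Detectable d = 0.317.

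**Step 3: adjusted for the 1-week score.** The residual SD is SD × √(1 − r²), so SE and detectable d both shrink by √(1 − r²). The equivalent unadjusted arm size is 157/(1 − r²).

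| r (assumed) | Variance removed (r²) | SE | Detectable d | Equivalent n per arm |
|---|---|---|---|---|
| 0 | 0 | 0.113 | 0.317 | 157 |
| 0.3 | 9% | 0.108 | 0.303 | 173 |
| 0.5 | 25% | 0.098 | 0.275 | 209 |
| 0.7 | 49% | 0.081 | 0.227 | 308 |

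For an illustrative true effect of 0.20 SD, power (normal approximation) rises from 42.5% to 45.9%, 53.4% and 69.9%. With 168 per arm, detectable d goes from 0.307 to 0.292, 0.265 and 0.219, so the conclusion does not depend on which n is used.

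**Step 4: chance imbalance.** The 95% range of the 1-week difference between arms is ±1.96 × 0.113 = ±0.22 SD. Multiplied by r, it carries ±0.07, ±0.11 or ±0.15 SD into an unadjusted 16-week estimate.

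**Step 5: which outcomes qualify.** The figures above are for the CES-D. The romantic-relationship scales are answered only by mothers with a current partner (section 6.a, Stress-Support Moderators), so the factor √(1 − r²) applies to a smaller n that the documents do not give. The coparenting scale has no 1-week value in Table 1, so no such gain is available.

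**The case against.** **The plan is silent and does not exclude adjustment.** It permits covariates in all models, the list is illustrative, and an exploratory analysis often gets its full model later. This stands in part. A reader might infer that the plan commits to an unadjusted test, and the text does not say that. But a permissive clause whose named factors are demographic, weight-related and intervention-related does not supply the outcome's own 1-week score. It also leaves the choice open until data are seen.

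**The 1-week score may not be a clean baseline.** This stands. Home Visit 1 lists randomisation and arm-specific materials before the questionnaires. If that order is followed, the score is post-randomisation. Any early effect of the materials may well be small, but a model that forces equal 1-week means across arms would not be justified.

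**Coverage is narrower than maternal functioning as a whole.** This also stands. A reader might infer that every relationship measure has a 1-week counterpart; coparenting does not. Romantic scales are paired only for mothers partnered at both visits, and the partner could differ between them.

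**Chance imbalance is not bias.** Correct. A reader might infer that the unadjusted estimate is biased. Under randomisation it is not biased on average, and its standard error already reflects the imbalance. The loss is one of precision.

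**Conclusion.** The point holds in a limited form. For the CES-D, and for the romantic-relationship scales among mothers with paired scores, the plan names no adjustment for a 1-week value that it collects. Run as written, the comparison is less precise than it could be. With about 157 per arm, the detectable CES-D effect falls from about 0.32 SD to 0.30, 0.275 or 0.23 SD at r = 0.3, 0.5 or 0.7. The size rests on r, which is assumed, and on 10% attrition from 175 per arm. At r = 0.3 the gain is small.

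Taking 80% power at d = 0.34 as the starting point would be tempting, but the current group size does not support it: 157 per arm already gives about 85%. Severity is low. The analysis is labelled exploratory, and no primary inference depends on it.

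**What to change.** Add to section 7.a, at the exploratory analysis:

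- The 16-week CES-D is analysed by ANCOVA, with arm and 1-week CES-D as terms, or by an equivalent mixed model with the 1-week score as covariate.
- The romantic-relationship scales are analysed in the same way among mothers with paired scores, with the number paired reported by arm.
- The coparenting comparison is unadjusted, because Table 1 has no 1-week value. Aim 3 treats coparenting as a 1-week moderator, so that text and Table 1 need to be reconciled.

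In section 6.a, state that the 1-week questionnaires are completed before allocation is revealed and materials are handed over, if that is the practice. If it is not, say so, and do not constrain the 1-week means to be equal across arms.

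The cost is two or three sentences and, where needed, a change to the order of steps at Home Visit 1. No new measurement is required.

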#### 4. Number of Subjects/Records/Samples Collected

*Indicate the total number of subjects to be accrued/records reviewed/samples collected across all sites:*

Up to 375 mother-infant dyads and up to 375 fathers will participate in the study. All mothers will complete a series of questionnaires at enrollment and at 4 follow-up time points (study procedures described below). AU medical records will be used to gather selected demographic information on mothers (race, maternal age, gestational age, weight at delivery, address) and infants (date of birth, weight and length at delivery). Fathers will be invited to participate by the recruitment coordinator if they are present at the hospital, or by the study team if they are present at the first home visit (1 week postpartum). Fathers will sign separate consent form.

The study will be conducted over 4 years. The table below details the number of target participants per year:

| Year         | Mother-Infant Dyads | Fathers (Max #) | Research Interactions |
|--------------|---------------------|-----------------|-----------------------|
| Year 1       | 50                  | 50              | 200                   |
| Year 2       | 125                 | 125             | 500                   |
| Year 3       | 125                 | 125             | 500                   |
| Year 4       | 75                  | 75              | 300                   |
| Total | 375          | 375      | 1500           |

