
|                                                                                                                                                                                                                                                                                                                                                                                                                                                                                                                                                                                                                                                                                                                                                       |                                 |
|-------------------------------------------------------------------------------------------------------------------------------------------------------------------------------------------------------------------------------------------------------------------------------------------------------------------------------------------------------------------------------------------------------------------------------------------------------------------------------------------------------------------------------------------------------------------------------------------------------------------------------------------------------------------------------------------------------------------------------------------------------|---------------------------------|
| 
The primary outcomes for this study will be BMI z scores at 16 weeks (Specific Aim 1) and parent and infant behaviors at 8 weeks and 16 weeks (Specific Aim 2). We used G Power 3.1.9.2 to estimate the smallest intervention effect size we can detect with 80% power, a 5% two-tailed Type 1 error rate, and two groups of 175 each (conservatively assuming 10% attrition over the course of the study). We can achieve 80% power with an effect size <math>d</math> of 0.34. Our recent research showed an effect size of approximately 0.4 for infant nighttime sleep duration at 8 weeks and for infant conditional weight gain at 6 months, suggesting that we will have sufficient power in our sample to detect intervention effects.
 |                                 |

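### BMI z and seven behaviour domains are all labelled primary under a single 5% error rate, with no order, adjustment or rule for a positive trial

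*Supplement*

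**What the plan says.** All references are to the latest protocol version in the Supplement, section 7 (Data and Specimen Management).

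- **Power analysis (7b).** The study's primary outcomes are "BMI z scores at 16 weeks (Specific Aim 1) and parent and infant behaviors at 8 weeks and 16 weeks (Specific Aim 2"). The calculation uses "80% power, a 5% two-tailed Type 1 error rate, and two groups of 175 each", and its detectable effect of d = 0.34 is offered as sufficient for the intervention effects in general.
- **Specific Aim 2 (7a).** "In Specific Aim 2 the primary outcomes are parental behaviors (parental self-efficacy, sleep/soothing practices, feeding practices, family chaos"), together with infant sleep, soothing and feeding. That is four parental and three infant domains, compared between groups at 8 and 16 weeks with a linear mixed-effects model. The results also decide which variables go forward to the mediation analysis.
- **Specific Aim 1 (7a).** "In Specific Aim 1 the primary outcomes are infant weight and changes in weight". The same paragraph then picks BMI z as the primary outcome, with other weight indices also modelled.
- **Table 1 (section 6).** The family-chaos scale is scheduled at 8 weeks only.

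The latest version gives no testing order, alpha split, gatekeeping, global test or multiplicity adjustment. It also has no rule for which outcomes must succeed for the trial to be called positive.

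**The concern.** The power section speaks at study level and puts the behaviours on the same footing as BMI z. A team following it as written could find BMI z null, find one behaviour nominally significant at one visit, and report a positive primary outcome without departing from the plan. The 5% stated in the power section is not the error rate of that claim.

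The power sentence has the mirror problem. It uses one unadjusted 5% for every outcome labelled primary, so any later adjustment would make it untrue for the behaviours.

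**Working it through.** **The plan's own figure.** Detectable d = (z for two-sided α + z for 80% power) × √(2/n per group).

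- 175 analysed per group: (1.960 + 0.842) × √(2/175) = 0.300.
- 175 less 10% attrition, 157.5 per group: 2.802 × √(2/157.5) = 0.316.
- The stated 0.34 therefore does not reproduce from the current inputs. It fits 135 per group (0.341), which is 150 × 0.9, the group size in the superseded version. This is a separate matter. Below I use 0.30–0.32 as the unadjusted baseline.

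**How many tests.** The documents do not fix the count, so I took two readings with one score per domain.

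- *One test per domain.* The Aim 2 mixed model lists group and infant weight but no time term, so a single group effect across visits is a natural reading. 7 domains + BMI z = 8 tests.
- *One test per domain per visit.* 7 × 2 = 14, less 1 because family chaos is measured only at 8 weeks, gives 13. Adding BMI z gives 14 tests.

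**Chance of at least one false positive, every test at 5% and no true effect.** If independent, this is 1 − 0.95^k. For correlated tests I simulated equicorrelated normal statistics (400,000 draws). The correlations are assumptions, since the documents give none.

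| Tests (k) | Correlation 0 | 0.3 | 0.5 |
|---|---|---|---|
| 8 | 1 − 0.95^8 = 34% | 30% | 25% |
| 14 | 1 − 0.95^14 = 51% | 44% | 35% |

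BMI z as the only primary test gives 5%. Even one test per aim gives 1 − 0.95² = 9.8%. At correlation 0.9, 14 tests still give 14%.

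**Price of adjusting within Aim 2.** Holm's first step tests the smallest p-value at 0.05/k.

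| Aim 2 tests | First-step α | z | Detectable d, 175 per group | Detectable d, 157.5 per group |
|---|---|---|---|---|
| 7 | 0.0071 | 2.690 | (2.690 + 0.842) × 0.1069 = 0.38 | 3.532 × 0.1127 = 0.40 |
| 13 | 0.0038 | 2.891 | (2.891 + 0.842) × 0.1069 = 0.40 | 3.733 × 0.1127 = 0.42 |

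The protocol's cited effect is about 0.4, so 7 tests sit at or just below it and 13 tests sit at or just above it.

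**The case against.** - **BMI z is already called the primary outcome.** It is, but within Aim 1, to choose among weight indices. That sentence does not rank BMI z above the Aim 2 outcomes, and the Aim 2 text and the power section both give those the same label. What stands is that the BMI z test alone has a 5% error rate. A reader might infer that the trial's weight conclusion itself is compromised; the documents do not support that.
- **Separate aims need no shared error budget.** This is partly a matter of judgement, and the plan never says that any single behaviour makes the trial positive. But it sets no other rule, and it pools the aims in one study-level list. Within Aim 2 alone, 7 tests give 1 − 0.95^7 = 30% and 13 give 1 − 0.95^13 = 49% if independent.
- **The 5% per test is inferred, and no separate analysis plan is shown.** Both are true. The level appears once, in the power calculation, and an adjustment could be set out elsewhere. The plural primary label, however, is positive text in this document and needs correcting here.
- **The count could be lower.** It could. Table 1 lists the Babies Need Soothing scale as infant soothing, while the measure's description covers parents' soothing practices, so two domains may share one instrument. It could also be higher: infant sleep has both parent report and actigraphy at 8 weeks. Hence a range, not one figure.
- **Chance findings would flow into mediation.** A reader might infer that a false-positive behaviour is enough to produce a mediation claim. The plan also requires an effect on the distal outcome and tests the indirect effect separately (Sobel or bootstrap), so this harm is limited.

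**Conclusion.** The point holds at the level of the study's primary family. As written, BMI z at 16 weeks and seven behaviour domains share the primary label and one stated 5%. Under no effect, the chance of at least one false-positive primary result is 25–34% (8 tests) or 35–51% (14 tests).

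These ranges assume one score per domain, every test at 5%, and equal correlations between 0.5 and 0. The exact size depends on choices the plan leaves open. The direction does not, unless one outcome is singled out or the tests are ordered or adjusted.

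**What to change.** In section 7a (Aims 1 and 2) and section 7b:

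1. Name BMI z at 16 weeks the single study-level primary outcome, tested at two-sided 5%.
2. Make weight change, rapid weight gain and the Aim 2 behaviours secondary, with one pre-named score per construct.
3. For Aim 2, either adjust within the family (for example Holm over one test per construct) or report the results with estimates and intervals and no confirmatory claim.
4. Limit the power statement to BMI z.

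This is a wording change: no added participants, visits or measurements, and the BMI z test is untouched. The cost is that the behaviours lose primary status. If Holm is chosen, the behaviours also pay the first-step price worked out above. That favours one test per construct, or the non-confirmatory route, over adjusting 13 visit-specific tests.

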| 
b. When applicable, provide a power analysis:
 
Power
 
The primary outcomes for this study will be BMI z scores at 16 weeks (Specific Aim 1) and parent and infant behaviors at 8 weeks and 12 weeks (Specific Aim 2). We used G Power 3.1.9.2 to estimate the smallest intervention effect size we can detect with 80% power, a 5% two-tailed Type 1 error rate, and two groups of 150 each (conservatively assuming 10% attrition over the course of the study). We can achieve 80% power with an effect size <math>d</math> of 0.34. Our recent research showed an effect size of approximately 0.4 for infant nighttime sleep duration at 8 weeks and for infant conditional weight gain at 6 months, suggesting that we will have sufficient power in our sample to detect intervention effects.
 | 
N/A |
| 
c. Describe how data and specimens will be handled:
                                                                                                                                                                                                                                                                                                                                                                                                                                                                                                                                                                                                                                                                                                                                                                     | 
N/A |

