### 3. Inclusion and Exclusion Criteria

*List the inclusion/exclusion criteria:*

A total of 375 African American mother-infant dyads will be recruited from AU's newborn nursery. Co-participation of the mother-infant dyad is a study requirement. Paternal involvement is voluntary, but not necessary. If fathers are interested in participating, they will sign separate consents.

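### The detectable effect size of d = 0.34 does not follow from two groups of 175 (it is about 0.32 or 0.30), and the step from 375 enrolled to 350 in the power statement is not explained

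*Supplement*

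**What the plan says.** The Supplement holds two versions of the protocol, and the later one governs. Its section 7b names BMI z score at 16 weeks as the Aim 1 primary outcome. It uses G Power to find "the smallest intervention effect size we can detect with 80% power", with "a 5% two-tailed Type 1 error rate". The sample and the claim read: "two groups of 175 each (conservatively assuming 10% attrition over the course of the study). We can achieve 80% power with an effect size"; the value given is d = 0.34. The paragraph then cites effects of about 0.4 from the team's recent research and concludes that power is sufficient.

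On enrolment, section 3 of the same version states: "A total of 375 African American mother-infant dyads will be recruited". Section 4 gives 375 as a maximum. Under section 6a, dyads are enrolled in the newborn nursery and randomised at the first home visit, 7 to 10 days postpartum. No section says how many of the 375 are expected to be randomised.

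The superseded version had a target of 300 dyads. Its power paragraph reads "two groups of 150 each (conservatively assuming 10% attrition over the course of the study" and reports the same d of 0.34.

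**The concern.** The paragraph gives every input that the calculation needs. Because d is standardised, no standard deviation has to be assumed, so the stated result should reproduce, and it does not. The group size rose from 150 to 175 between versions while the detectable effect stayed at 0.34, although a larger sample must detect a smaller effect.

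This is the only statement of planned sensitivity for the primary outcome. A reader who uses it to interpret a small or null difference would be working with a detectable effect that belongs to a smaller sample. The unexplained step from 375 to 350 adds to the difficulty, because the reader cannot tell what number the 10% attrition applies to.

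**Working it through.** **Inputs** (latest version, section 7b unless noted): two-sided alpha 0.05; power 0.80; 175 per group; attrition 10%; stated d = 0.34; enrolment up to 375 (sections 3 and 4). From the superseded version: 150 per group, 300 dyads, 10% attrition, d = 0.34.

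**Method.** Two-sample comparison of means, 1:1. The normal approximation is d = (z₀.₉₇₅ + z₀.₈₀) × √(2/n) = (1.960 + 0.842) × √(2/n), with n analysed per group. The noncentral t solution, which is the G Power t-test method, is given beside it.

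**Step 1: try to reproduce 0.34 from the current version.**

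| Reading | n analysed per group | d, normal | d, noncentral t | Power at d = 0.34 | Power at d = 0.4 |
|---|---|---|---|---|---|
| 175 before attrition | 175 × 0.9 = 157.5 | 0.316 | 0.317 | 85.3% | 94.3% |
| 375 randomised, less 10% | 375 × 0.9 / 2 = 168.75 | 0.305 | 0.306 | 87.6% | 95.6% |
| 175 analysed | 175 | 0.300 | 0.300 | 88.7% | 96.2% |
| 375 with no loss | 375 / 2 = 187.5 | 0.289 | 0.290 | 90.7% | 97.2% |

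None gives 0.34. A one-sided test with 175 per group gives 0.266, which is further away. At 90% power, 175 per group gives 0.348 and 187.5 gives 0.336, but the text states 80%.

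**Step 2: find the sample that 0.34 does fit.** n = 2 × (2.802 / 0.34)² ≈ 135.8, so 136 per group by the normal approximation and 137 by noncentral t.

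**Step 3: compare with the superseded plan.** 300 × 0.9 / 2 = 135 per group, which gives d = 0.342 and rounds to 0.34. Without attrition, 150 per group would give 0.325. So 0.34 belonged to 150 per group *after* the 10% loss. This suggests that the authors quote the group size before attrition and compute d after it. On that convention the current figure is the first row of the table, d of about 0.32.

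**Step 4: check the link between 375 and 350.** 2 × 175 = 350.
- 1 − 350/375 = 6.7%, not 10%.
- 375 × 0.9 = 337.5, about 168 per group, not 175.
- To keep 350 after a 10% loss, 350 / 0.9 ≈ 389 dyads would have to enter.

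No single 10% loss connects the two numbers, and the text gives no other step.

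**The case against.** **The stronger reading of the arithmetic.** A reader might infer that 0.30 is simply the right answer and that 175 is a failed attempt to take 10% off 375. The documents do not support either inference firmly. The superseded version's figures point to 175 being a count before attrition, which makes the gap 0.34 against about 0.32 and not 0.30. Section 7b never claims to derive 175 from 375. Since 375 is a ceiling and randomisation comes about a week after nursery enrolment, enrolling up to 375, randomising 350 and then losing 10% is a coherent plan. It is not written down. The section 4 table does not settle it: its 1,500 interactions are 375 × 4, which counts every dyad at every home visit with no loss at all. What stands is that the link is unstated, not that a subtraction is wrong.

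**The stronger reading of the consequence.** A reader might infer that the trial is underpowered or that the sample size must change. The reverse holds: the planned sample detects a smaller effect than the text claims.

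**Is the figure worth correcting?** The 16-week model adjusts for 1-week weight, so a t-test d is only a planning figure, and a finished trial is read mainly from its confidence interval. This limits the importance of the point. It does not make the stated figure right, since no reading of 175 or 375 returns 0.34 at the stated power and alpha.

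**Carry-over.** That 0.34 was left from the 300-dyad plan is an inference from a numerical match, and should be put no more strongly.

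**Conclusion.** The stated detectable effect is wrong for the stated inputs. At 80% power and two-sided 5%, d is about 0.32 if 175 per group is before the 10% attrition, which is the more natural reading, or 0.30 if 175 are analysed. The error in d is therefore 0.02 to 0.04. Separately, the relation between up to 375 enrolled and 350 in the power statement is not given.

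This rests on an unadjusted two-sample comparison with equal allocation, as the paragraph's own wording implies. The choice between 0.32 and 0.30 rests on a convention inferred from the superseded version.

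The paragraph's conclusion survives: power for an effect of about 0.4 is roughly 94% to 96% with 157 to 175 analysed per group. This is a minor correction to a stated figure, not a threat to the trial.

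**What to change.** Rewrite the power sentence so that the enrolled, randomised and analysed numbers stand on one basis, and replace 0.34 with the d that matches. The authors should choose the basis, since the documents do not fix it:

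- 350 randomised, less 10% (about 157 per group analysed): d = 0.32
- 375 randomised, less 10% (about 168 per group analysed): d = 0.31
- 175 per group analysed: d = 0.30, stating how many dyads must be randomised to reach that number

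The sentence should also say whether 375 counts dyads enrolled in the nursery or dyads randomised at the 1-week visit and, if the former, what loss is expected between the two. The cost is a sentence or two of text. Enrolment and the analyses do not change.
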